### Participants and Recruitment Strategy

#### Eligibility Criteria

The inclusion criteria for healthy controls (the group without cognitive impairment) are as follows: (1) males and females aged ≥19 years without cognitive impairment (MMSE-K≥24, K-MoCA≥23); (2) participants without severe neurological, organic dysfunction; and (3) participants or authorized surrogates who voluntarily sign the informed consent.

The inclusion criteria for the group with cognitive impairment are as follows: (1) males and females aged ≥60 years showing cognitive impairment (MMSE-K<24, K-MoCA<23) or diagnosed with mild cognitive impairment (MCI) or dementia with a clinical dementia rating<3; (2) participants or authorized surrogates who voluntarily sign the informed consent; and (3) participants who can complete this study.

The exclusion criteria for healthy controls (the group without cognitive impairment) are as follows: (1) participants with other brain disorders, alcoholism or drug abuse, neuropsychiatric disease, or taking psychiatric medicines, and severe organic dysfunctions inducing cognitive impairment; and (2) participants with any other reasons that may be considered inappropriate by the researcher.

The exclusion criteria for the group with cognitive impairment are as follows: (1) severe dementia patients with a clinical dementia rating of 3; (2) patients with other brain disorders such as cerebrovascular disease and epilepsy; (3) patients with cognitive impairment induced by another primary disease; (4) patients with severe organic dysfunctions; (5) patients presenting alcoholism or drug abuse, with neuropsychiatric disease or taking psychiatric medicines; and (6) patients with any other reasons that may be considered inappropriate by the researcher.

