#### Enrollment, Randomization, and Blinding

Recruitment will be conducted through advertisements on websites and public announcements. Promotion through local communities is also under consideration. The recruitment of participants with cognitive impairment will be promoted through cooperation with community dementia care centers. In this study, in accordance with the recruitment of the participants, the effect of age on brain function will also be investigated; therefore, recruitment in the group without cognitive impairment will not be restricted to older adult participants.

Stratified block randomization will be performed according to sex. Both groups will be assigned in a 1:1 ratio to the study and control groups by applying a block size of 4. Randomization will be conducted using a computer-generated allocation list by an assigned researcher not involved in the assessment or intervention. Participants will be blinded to the type of intervention used. The practitioner will not provide clues regarding allocating information to the participants during the study. Blinding will be maintained until the end of the study. Participants will be asked about their experience of blinding after the end of the study.

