#### Measurement of Cognitive Reserve

CR assessment will be conducted using the CRIq questionnaire [32]. It includes demographic data and items categorized into 3 sections: education, working activities, and leisure time; each item returns a subscore. It evaluates the CR of an individual by compiling the information associated with the individual’s entire adult life. The quantification of CR will be calculated as the sum of all domains, and the subscore of each domain will also be applied in further correlation analysis. Depending on the mean value of CRIq, it will be dichotomized into the high CR and low CR groups. The investigator will also assess the participants’ bilingualism. The evaluation of each assessment will be conducted by an investigator blinded to the assigned group.

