### Statistical Analysis

Only data from participants who completed the fNIRS scan, cognitive function test, and measurement of CR will be contained in the statistical analysis. All categorical data are presented as frequencies or percentiles and will be analyzed using the chi-square or Fisher’s exact test. All numerical data will be presented as the mean and standard deviation and analyzed using an independent *t* test or Wilcoxon rank-sum test. Preprocessing and analyses of fNIRS data will be performed using MATLAB and the NIRSIT analysis tool.

A two-sample *t* test will be performed to compare the brain activations and connectivity between the groups with and without cognitive impairment. A paired *t* test will be conducted to compare the brain activations and connectivity before and after acupuncture stimulation. The CR values from CRIq will be applied for correlation analysis in the form of continuous variables or divided into binary groups (high and low CR) by mean values for subgroup analysis. Since the expression of CR may appear differently depending on the disease status, a subgroup analysis will be conducted by dividing the healthy control and the patient group. Mixed model analysis will be adjusted to determine the interaction effect of intervention and CR in both groups. Pearson correlation will determine the CR-related brain connectivity or clinical score–related metrics. If there is a significant age difference between 2 groups, the age factor will be added as a covariate in the analysis to adjust the effect of age as much as possible.

Statistical significance in fNIRS imaging would be explored using uncorrected and corrected levels (false discovery rate and family-wise error). At the uncorrected level, uncorrected *P*<.001 will be used, and at the corrected level, *P*<.05 will be applied.

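### Eligibility ties age to disease status (60 or over versus 19 or over), yet the protocol adjusts for age only if an age test between two unnamed groups is significant

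*Protocol article*

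**What the plan says.** The Eligibility Criteria admit to the unimpaired group "males and females aged ≥19 years without cognitive impairment" and to the impaired group "males and females aged ≥60 years showing cognitive impairment" (or with a diagnosis of mild cognitive impairment or dementia). The difference is deliberate. Under Enrollment, Randomization, and Blinding the protocol explains that "the effect of age on brain function will also be investigated", and that "recruitment in the group without cognitive impairment will not be restricted to older adult participants". No age matching is described, and the only stratification factor is sex: "Stratified block randomization will be performed according to sex".

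Under Outcome Measures, primary outcome 1 compares impaired with unimpaired participants and primary outcome 3 compares high with low CR. Neither contrast is randomized. For the first, the Statistical Analysis section says that a two-sample *t* "test will be performed to compare the brain activations and connectivity between the groups with and without cognitive impairment". CR is analysed as a mean split or by Pearson correlation, with a subgroup analysis within controls and patients. Age enters by one sentence: "If there is a significant age difference between 2 groups, the age factor will be added as a covariate in the analysis".

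**The concern.** Age is a confounder that this design creates. Eligibility links it to disease status, and the protocol itself treats it as something that may act on brain function. Randomization between verum and sham gives the disease-status contrast no protection. For a confounder known in advance, a preliminary significance test is a poor trigger, because its result depends on sample size and not on how much bias the imbalance causes.

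The rule also fails to name its two groups. The Abstract and the Trial Design section speak of two groups meaning verum and sham. The sentences around the rule deal with controls and patients. Both readings are open, and they lead to very different analyses.

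Two of the three primary outcomes are at stake. A difference reported as disease-related could be partly or wholly an age difference. The stated interest is in normal aging, which a control group open to 19-year-olds need not represent.

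**Working it through.** The protocol gives no age distribution and no age slope, so there is no figure of its own to reproduce. Group sizes are from the document: 30 and 30 planned (Abstract), 20 impaired and 30 unimpaired to date (Results). All age inputs below are assumptions. Rates are for one measure at two-sided 5%. The imaging thresholds in the Statistical Analysis section (uncorrected *P*<.001, or corrected *P*<.05) would give lower rates per channel, but the bias would be the same.

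**1. Bias if age is ignored.** Assume no disease effect, a mean age gap of 20-30 years and a slope of 0.2 SD per decade.
- Spurious d = 2 × 0.2 = 0.4, or 3 × 0.2 = 0.6.
- Noncentrality = d × √(30/2): 0.4 × 3.87 = 1.55, or 0.6 × 3.87 = 2.32.
- With 58 degrees of freedom, the chance of significance is 33% or 63%.

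**2. Reading A: the two groups are impaired and unimpaired.** Assume an age SD of 15.
- Gap of 20 years: 20/15 = 1.33 SD, so the age test is significant 99.9% of the time. Gap of 30 years: 2.0 SD, about 100%.
- Age is therefore added. In simulation with a linear age effect, the conditional rule gives about 5% false positives, the same as always adjusting.
- Gap of 8 years: 8/15 = 0.53 SD, detected 53% of the time at 30 v 30 and 44% at 20 v 30. The spurious d is only 0.8 × 0.2 = 0.16, which gives about 9% unadjusted and about 5-6% under the conditional rule.

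So the gaps that the age test misses are those that cause little bias.

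**3. Reading B: the two groups are verum and sham.** These arms are randomized, so an age difference between them is significant about 5% of the time by chance. The disease contrast then usually stays unadjusted, and the 33-63% of step 1 applies.

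**4. What adjustment leaves behind.** No impaired participant is under 60 unless a diagnosed patient falls outside the stated age limit. Simulations with 30 v 30, impaired aged 60-85, no disease effect and age-outcome correlation 0.3 or 0.5:

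| Assumed control ages | Unadjusted | Always adjusted | SE, unadjusted → adjusted |
|---|---|---|---|
| 19-85 | 23-58% | 4-5% | 0.26-0.29 → 0.32-0.33 |
| 19-60, linear age effect | 54-96% | 5% | 0.26-0.27 → 0.51 |
| 19-60, age effect only after 55 | 52-95% | 7-12% | 0.26-0.27 → 0.52-0.53 |

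In the last row a bias of 0.2-0.4 residual SD remains after adjustment. It comes from extrapolating a straight line across ages with no impaired participants.

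**5. CR contrast.** The Measurement of Cognitive Reserve section says of the questionnaire: "It evaluates the CR of an individual by compiling the information associated with" the whole of adult life, and the score is a sum of domains. Assume a CR-age correlation of 0.2-0.5 within 30 controls and no CR effect. The unadjusted mean split is falsely significant in 6-18% of runs. An age test between high and low CR would be significant in 13-62% of runs, and applying the rule to those groups gives 5-6%.

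**The case against.** A reader might infer that the conditional rule by itself leaves a 33-63% false-positive rate. On reading A the documents do not support that: a gap wide enough to cause such bias is almost certain to trigger the adjustment. The large figures need reading B.

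A reader might also infer that a disease difference would be entirely an age difference. The protocol permits younger controls but does not say how many there are. Results gives counts, sex and diagnosis, and no ages. The extent of poor overlap is therefore unknown.

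It is tempting, too, to say that outcome 3 has the same confounding by construction. How the questionnaire is scored lies in a cited source, and a condensed article that does not mention age standardization does not show there is none. The planned subgroup analysis within controls and within patients also separates CR from disease status, though the controls still span ages from 19.

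Lastly, limiting the primary contrast to controls aged 60 or over has its own price. If control ages averaged 55 (SD 15), about 37%, or 11 of 30, would remain, and the variance would rise by (1/11 + 1/30)/(2/30) = 1.86. Adjusting for age over all ages, with impaired ages assumed around 75 (SD 6, truncated at 60), inflates it about 1.8-fold (group-age correlation 0.66; 1/(1 − 0.66²) ≈ 1.8). Restriction is thus no cheaper than adjustment.

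These points limit the size of the concern. They do not rescue a rule that leaves its groups unnamed and makes adjustment for a design-built confounder depend on a test. The authors do recognise age as a confounder, which makes the repair uncontroversial.

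**Conclusion.** The concern holds. Age is tied to disease status by eligibility, and the one sentence that deals with it is badly fixed.

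Its size depends on the reading. With impaired versus unimpaired as the trigger, wide gaps are adjusted almost always and false positives stay near 5% if the age effect is linear. The residue is extrapolation below 60: 7-12% false positives and a doubled standard error in the assumed no-overlap, non-linear case. With verum versus sham as the trigger, the disease contrast would usually go unadjusted, with 33-63% false positives under the assumed gap and slope.

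An age component in the CR contrast is plausible but inferred, and probably smaller (6-18% unadjusted under the assumed correlations). The randomized verum versus sham comparison is not confounded in this way.

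**What to change.** Replace the conditional sentence with one to this effect: age will be a covariate in all models for disease status and for CR, including the subgroup models, whatever the result of any test of age differences. This also removes the ambiguity about the two groups.

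Add a prespecified disease-status comparison limited to participants aged 60 or over, and require any conclusion about disease status to be consistent with it. Younger controls stay in the all-ages model and serve the separate question about age. Report the age distribution of both groups so that readers can judge the overlap.

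Age is already collected, so no new participants or measurements are needed. The cost is one degree of freedom, a wider interval for the adjusted effect (about 1.8-fold variance in the assumed example), and fewer controls in the 60-or-over comparison (about 11 of 30 in that example).

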#### fNIRS Imaging

For this experiment, fNIRS equipment (NIRSIT, OBELAB) will be used. fNIRS is a portable near-infrared neuroimaging device that measures hemodynamic variations in cerebral blood by irradiating the cerebral cortex with a near-infrared laser. The equipment irradiates the wavelengths of 780 and 850 nm of laser, which is harmless to humans. It contains 48 channels that can cover the frontal regions of the brain, allowing the quantification of ΔHbO_2_, ΔHbR, and ΔHbT in that area. Based on this, the analysis applied in fMRI, such as graph theory analysis and general linear model analysis, can be used.

The fNIRS scans will be conducted before and after acupuncture. The scan consists of 2 parts: a resting state and working memory task scan. The resting-state fNIRS scan lasts for 5 minutes, during which the participant is asked to look at the monitor screen and remain comfortable. The task fNIRS scan is performed while conducting a Corsi block tapping task, a cognitive task related to working memory [33]. This experiment requires participants to tap a spatially separated sequence of up to 9 identical blocks in the same order in which they are presented. The sequences start simple, using 4 blocks, and become more complicated using a maximum of 6 blocks (Figure 2).

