### Outcome Measures

This study aims to explore the immediate neural mechanisms of the acute response to acupuncture stimulation associated with CR in normal aging and disease status and identify the neural substrates of CR.

The primary outcomes will be as follows: (1) differences in brain activation and resting-state brain connectivity according to disease status (the groups with vs without cognitive impairment); (2) differences in brain activation before and after acupuncture between study and control groups (verum acupuncture vs sham acupuncture); and (3) differences in brain activation according to CR (high CR group vs low CR group).

Secondary outcomes are brain connectivity or network metrics (graph theoretic metrics) associated with the CRIq index, differences in brain activity between working memory tasks and resting states, and network metrics associated with cognitive function scores (MMSE-K, K-MoCA).

The brain connectivity matrix will be obtained as Pearson correlation between 48 channels using time-series data during the scan period (Figure 3). Network metrics, including the index of efficiency, clustering coefficient, and centrality, can be calculated using the connectivity matrix by the Brain Connectivity toolbox in MATLAB 2023b (The Mathworks).

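### Uncorrected P<.001 stands beside FDR and FWE with no rule for which decides; over 1,128 connectivity edges it expects 1.13 false positives per contrast

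*Protocol article*

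**What the plan says.** The Statistical Analysis section of the protocol article sets the imaging thresholds in two sentences. The first reads "Statistical significance in fNIRS imaging would be explored using uncorrected and corrected levels (false discovery rate and family-wise error". The second gives the values: "At the uncorrected level, uncorrected *P*<.001 will be used", and "at the corrected level, *P*<.05 will be applied". That is three criteria for the same maps (uncorrected, FDR and FWE), and no section ranks them.

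Connectivity is defined under Outcome Measures: "The brain connectivity matrix will be obtained as Pearson correlation between 48 channels using time-series data during the scan period". It enters the analysis in three places:

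- Outcome Measures, primary outcome 1, covers "1) differences in brain activation and resting-state brain connectivity according to disease status".
- The Abstract words the verum-sham primary outcome as a pre/post difference in resting connectivity. Outcome Measures words the same outcome as activation.
- Statistical Analysis applies both the two-sample t test (disease status) and the paired t test (before and after stimulation) to activation and to connectivity.

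Primary outcomes 2 and 3, as worded in Outcome Measures, concern activation only.

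**The concern.** A threshold of P<.001 looks strict, but its strictness depends on how many tests it is applied to. Over an edge-wise connectivity matrix it allows more than one chance result per contrast on average. Because the text offers this level alongside the corrected ones and makes none decisive, a map that fails both FDR and FWE could still be reported as significant.

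The Introduction's main hypothesis is that frontal connectivity changes with acupuncture, and the Conclusions look ahead to a scientific basis for clinical use. An isolated edge at uncorrected P<.001 could be presented as part of a mechanism when chance alone would be expected to produce one.

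**Working it through.** The article states no false-positive rate, so there is no figure of its own to reproduce. Its one computed design figure, the sample size, does not bear on this point.

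**Inputs**
- Channels: 48 (fNIRS Imaging; Outcome Measures).
- Uncorrected level: .001 per test (Statistical Analysis).
- Corrected level: .05, for FDR and FWE alike (Statistical Analysis).

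**Step 1: tests per contrast**
- Activation: 48 channels.
- Connectivity: 48 × 47 / 2 = 1,128 distinct edges. This count is derived; the article does not print it.

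**Step 2: expected false positives at uncorrected P<.001 with no true effect**

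Expected number = m × .001. Expectations add whatever the dependence, so this needs no independence assumption, only a valid P value for each test.
- Connectivity: 1,128 × .001 = 1.13.
- Activation: 48 × .001 = 0.048.

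**Step 3: chance of at least one, if tests are independent**

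P = 1 − (1 − .001)^m.
- Connectivity: 1 − .999^1,128 = 67.7%.
- Activation: 1 − .999^48 = 4.7%.

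**Step 4: comparison with Bonferroni**
- Activation: 0.05/48 = .00104, so .001 is already about family-wise 5%.
- Connectivity: 0.05/1,128 = .0000443, so .001 is about 23 times too lenient for family-wise 5% (.001/.0000443).

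**Step 5: effect of correlated edges**

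Edges of one matrix share channels, so independence is unlikely. A null simulation of 30 versus 30 participants, 500 runs per setting, used channel correlations that are assumptions, not figures from the article.

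| Assumed structure | Mean edges at P<.001 | At least one at P<.001 | At least one by FDR .05 | At least one by Bonferroni .05 |
|---|---|---|---|---|
| Spatial correlation | 1.02 | 44% | 5.0% | 4.8% |
| Spatial plus a strong subject-level global signal | 2.47 | 5.2% | 1.8% | 0.8% |

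In the second setting false positives are rare but come in clusters. All of them arose in 0.052 × 500 = 26 runs, at about 47 edges each (2.47/0.052). The mean of 2.47 therefore rests on few runs and is imprecise; the theoretical value remains 1.13.

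In both settings FDR and FWE hold the chance of any false finding at 5% or less, so the problem lies in the uncorrected level and not in the choice between the two corrections.

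**The case against.** **The text says significance will be explored, and corrected levels are named.** Both are true, and they soften the point: the article does not say that conclusions will be drawn from uncorrected maps. But the verb is attached to statistical significance, covers the primary outcomes, and leaves no level decisive.

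**A separate analysis plan may settle it.** It may. The point rests on a rule that the article does print. A later document would have to narrow that rule, not fill a gap.

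**The edge problem does not reach every primary outcome.** This stands. In Outcome Measures only primary outcome 1 names connectivity. The problem reaches the verum-sham comparison only through the Abstract's wording, and the pre/post analysis through the paired t test on connectivity. The difference between the Abstract and Outcome Measures is a separate matter to reconcile.

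A reader might also infer three stronger claims, which the documents do not support:

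- *That the lenient level will nearly always produce a significant connection.* The 68% assumes independence; under the assumed correlations it was 44% or about 5%.
- *That three haemoglobin signals triple the count to 3.4.* The device description speaks of "allowing the quantification of ΔHbO_2_, ΔHbR, and ΔHbT in that area", which is a capability. No section says that all three will be tested for the primary outcomes.
- *That listing three primary outcomes ("The primary outcomes will be as follows") at 5% each, 14.3% if independent, is itself an error that requires a single primary or a split of alpha.* The outcomes ask different questions, and nothing says that any one positive result makes the trial a success. Sharing error across them is a trade-off. Holm could not be applied directly, because each outcome is a map without a single P value.

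**Conclusion.** The point holds for edge-wise connectivity. As printed, the significance rule admits uncorrected P<.001 beside FDR and FWE without saying which decides, and at that level 1.13 false-positive edges are expected per connectivity contrast when there is no effect. That count needs only valid edge-wise P values. The 68% chance of at least one is an independence figure and falls with correlation, by an amount that the article's data cannot fix.

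The point does not extend to channel-wise activation within one contrast and one signal, where P<.001 is about Bonferroni. Nor does it show that the investigators intend to base conclusions on uncorrected maps; it shows that the stated rule would let them.

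**What to change.** In Statistical Analysis, replace the open list of levels with one deciding rule. For example: significance is decided by FDR q<.05 over all 1,128 edges of a connectivity contrast, and separately over all 48 channels of an activation contrast; maps at uncorrected P<.001 are descriptive only and support no conclusion. FWE at .05 over the same families would serve equally well if preferred, but one of the two should be named.

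The change needs no new data or participants and alters no primary outcome. It should be made before results are examined, because a criterion chosen afterwards does not restore the error rate. The cost is that fewer connections can be called significant. Primary outcome 1 would still contain two families, edges and channels, each at 5%, so the chance of any false finding across both could reach 2 × 5% = 10%; the text should say openly that they are treated separately.
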